### Data management

Participants will be allocated an anonymised unique identifier. Only the research team will be able to identify participants, using a key that links the unique identifier to an identifiable data field. Personal identifiers (i.e. the informed consent forms) will be stored separately from the main research data in a different cabinet. All electronic data relating to the study will be stored in an encrypted format, in a study-specific database accessible only to delegated members of the research team via a unique username and password.

### Data analysis

Any data collected during this study will available on request from the corresponding author ([name]). The data will not be made publicly available, in accordance with the General Data Protection Regulation (GDPR).

#### Quantitative data

Owing to the exploratory nature of this feasibility study, the sample size will be based on the pragmatic limits of recruitment. Since the primary aim of this study is to determine the feasibility of conducting a future RCT, a descriptive analysis will be performed to examine key feasibility and process-related outcomes. All quantitative data will be uploaded into SPSS^27^ for analysis, where recruitment, retention and follow-up rates at study completion will be quantified using absolute and relative frequencies and percentages of the overall population.

In particular, the percentage of potential participants who agree to undergo the screening assessment out of the total number of potential participants who were initially invited will be calculated. The percentage of the total number of participants who were enrolled into the study out of the total number invited will be calculated with a 95% confidence interval ±6%.

The main analysis will estimate the percentage of potentially eligible participants, consent and overall uptake. The retention, follow-up and outcomes rates will be calculated in relation to the number recruited. Engagement with the intervention will be described by the percentage of appointments attended as a proportion of booked appointments. An estimated engagement rate of approximately 90% (32/36 retained patients) will give a 95% confidence interval width of ±10%. Additional healthcare resources will be described by type and frequency of use in absolute numbers.

The means and confidence intervals of clinical outcomes will be calculated to determine their sensitivity to change. This will guide the identification of a primary outcome measure for a future RCT. In addition, we will determine the acceptability of the clinical outcomes by calculating percentage rates of completion for the PHQ-ADS, EQ-5D-3L, NPRS, PDI, MSK-HQ and the GRoC.

A detailed statistical analysis plan will be developed by the study statistician. To illustrate participant flow, we will report results using a CONSORT flow diagram.^23^

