### Sample size

As this study is a feasibility trial, all analyses will be descriptive, with no hypothesis testing. Consequently, no formal sample size calculation has been conducted. We aim to recruit 40 patients in total, with 20 randomised to each arm.

The study aims to recruit these patients over 3 months, with a target recruitment rate of 20% of all eligible patients. It is estimated that there may be at least 200 new eligible patients in 3 months. Assuming this number of eligible patients, the recruitment rate could be estimated within ±6% with a 95% confidence level.

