### Randomisation and allocation

The study will follow the Consolidated Standards of Reporting Trials (CONSORT) guidelines^23^ for the design and implementation of randomised controlled trials. The CONSORT extension for randomised pilot and feasibility trials is meant to provide reporting guidance for any randomised study in which a future definitive RCT, or part of it, is conducted on a smaller scale. After the consent and eligibility procedure, participants will be randomised in a 1:1 ratio (collaborative care:usual care). Allocations will be concealed and undertaken using online randomisation software^24^ by a member of the research team. Since this study aims to assess the feasibility of the CCM, which includes support from a case manager, it will not be possible to mask healthcare professionals or participants to the intervention.

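### The ±10% precision for engagement with the intervention is worked out on 36 patients from both arms and in patients, whereas the measure concerns the 20 CCM patients and is defined in appointments

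*Protocol article*

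**What the plan says.** Three statements in the protocol article bear on this point.

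- Sample size: "We aim to recruit 40 patients in total, with 20 randomised to each arm". Randomisation and allocation confirms the 1:1 ratio.
- Quantitative data, definition of the measure: "Engagement with the intervention will be described by the percentage of appointments attended as a proportion of booked appointments".
- Quantitative data, the next sentence, on its precision: "An estimated engagement rate of approximately 90% (32/36 retained patients) will give a 95% confidence interval width of ±10" (per cent).

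Primary and secondary outcomes lists adherence to the intervention among the co-primary outcomes. It lists engagement separately as a secondary outcome and names the CCM as what is engaged with. The Interventions section gives the case manager to the intervention arm only; the control arm receives usual therapy.

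**The concern.** The precision sentence follows directly on the definition of engagement with the intervention, so a reader takes ±10% as the precision with which CCM engagement will be known. Two things do not fit.

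First, the base of "32/36 retained patients" is larger than either arm. It has to include usual-care patients, who have no CCM to engage with.

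Second, the measure counts appointments while the precision counts patients. Appointments from one patient are not independent, so a patient-level binomial interval is not the interval for an appointment-level percentage.

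The trial tests no hypotheses, so how precisely it can estimate feasibility quantities is the main quantitative information it offers for planning the later trial. A planner relying on the ±10% would expect firmer knowledge of CCM engagement than 20 patients can give on the basis shown.

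**Working it through.** **Inputs**
- 40 patients, 20 per arm (Sample size).
- 32 engaged of 36 retained, about 90%, 95% confidence, ±10% (Quantitative data).
- Implied retention, not stated as such: 36/40 = 90%.
- CCM arm at the same rates: 20 × 0.90 = 18 retained; 18 × 32/36 = 16 engaged.

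**Formula.** The usual large-sample (Wald) half-width is h = 1.96 × √[p(1 − p)/n]. The plan's ± figure is a half-width, although the text calls it a width.

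**1. The plan's own figure**
- p = 32/36 = 0.889, n = 36: h = 1.96 × √(0.889 × 0.111/36) = 0.103.
- p = 0.90, n = 36: h = 1.96 × √(0.90 × 0.10/36) = 0.098.

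Both round to ±10%, so the figure reproduces on 36 patients.

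**2. The same calculation for the CCM arm**

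| Basis | Rate | Wald half-width | Wilson 95% | Exact 95% |
|---|---|---|---|---|
| 16/18 retained | 88.9% | ±14.5 points | 67.2% to 96.9% | 65.3% to 98.6% |
| 18/20 allocated | 90.0% | ±13.1 points | 69.9% to 97.2% | 68.3% to 98.8% |

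For 16/18, n is halved at the same p, so the half-width grows by √2: 10.3 × 1.414 = 14.5.

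**3. Patients needed for ±10 points**

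n = 1.96² × p(1 − p)/0.10².
- p = 0.90: 34.6, so 35 patients.
- p = 0.889: 37.9, so 38 patients.

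The CCM arm is planned at 20.

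**4. The appointment measure**

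With k patients, m booked appointments each and within-patient correlation ICC, h = 1.96 × √{p(1 − p)[1 + (m − 1)ICC]/(km)}. The article gives neither m nor ICC, so the values below are assumptions, with k = 18 and p = 0.90.

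| m | ICC = 0 | ICC = 0.3 | ICC = 1 |
|---|---|---|---|
| 3 | ±8.0 | ±10.1 | ±13.9 |
| 6 | ±5.7 | ±8.9 | ±13.9 |
| 10 | ±4.4 | ±8.4 | ±13.9 |

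On this measure ±10 points may or may not be met. The stated figure does not follow from anything in the article.

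**The case against.** The best defence is that both arms were meant. Feasibility outcomes includes an indicator on engagement with first and follow-up appointments that is not tied to an arm. That indicator is broader, but the precision sentence follows directly on engagement with the intervention, and the secondary outcome names the CCM. Pooling usual-care attendance would answer a different question.

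The other defences limit the point, and they stand.

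- **The arithmetic is sound.** ±10% is a correct Wald figure for 36 patients. The fault is the population and the unit. That an exact interval for 32/36 is asymmetric is no separate error.
- **Inflation is not shown.** A reader might infer that using retained patients or booked appointments as the denominator inflates the rate. The 90% is a planning value, not an estimate, and the article does not restrict the appointment measure to retained patients. It says only: "The retention, follow-up and outcomes rates will be calculated in relation to the number recruited". If neither of the two patients lost from the CCM arm engaged, the rate would be 16/20 = 80%; if both did, it would be 18/20 = 90%. The article gives no booking rule after disengagement from which to settle this.
- **The results are not thereby made falsely precise.** An anticipated half-width does not enter the analysis; the reported interval will come from the data observed.
- **The figure drove no decision.** Sample size states that there was no formal calculation and that the analyses are descriptive. No progression rule in the article rests on the ±10%.
- **The link to the co-primary outcome is an inference.** Adherence and engagement are listed separately, and the precision sentence speaks of engagement.

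**Conclusion.** The stated precision is wrong for the group it describes and uses a different unit from the measure it accompanies. With the patient as unit, the expected half-width for CCM engagement is about ±13 to ±14.5 points, not ±10. This rests on 20 patients allocated to the CCM, a rate near 90%, and, for the 16/18 figure, 90% retention in that arm as implied by 36 of 40.

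The shortfall is certain only on that patient basis. For attended out of booked appointments, ±10% is unsupported rather than shown to be missed. It would be tempting to conclude that the engagement rate will be biased upwards or that the trial will report misleading precision, but the article supports neither. This is a minor correction to one planning statement.

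**What to change.** Restate the expected precision for the CCM arm only (20 allocated, about 18 retained), with an exact or Wilson interval. For example, 18/20 gives an exact 95% interval of 68% to 99%, and 16/18 gives 65% to 99%.

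Use one unit for both the definition and the precision:
- a per-patient proportion over all patients allocated to the CCM, saying how those not retained are counted; or
- attended out of booked appointments in the CCM arm, with an interval that allows for clustering by patient and with the assumed visits per patient and correlation stated.

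If attendance in both arms is also of interest, report it as a separate, clearly labelled quantity. The change is to wording only and needs no extra patients or data. Its one cost is a less favourable stated precision.

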#### Qualitative data

Focus group and interviews will be transcribed in full (verbatim) by an external company, checked for accuracy by a member of the research team and then imported into NVIVO version 12 qualitative data analysis software,^28^ to aid management and indexing of data. Transcripts from the participants and healthcare professionals will be analysed separately. A subset of transcripts will be independently double coded by a member of the research team and compared. Discrepancies will be discussed with another member of the research team and resolved to achieve a coding consensus. The analysis will begin shortly after data collection starts. It will be carried out by one member of the research team using normalisation process theory (NPT).^29^ This type of analysis explains the processes by which complex interventions become routinely embedded in healthcare practice.^29^

This model is particularly important for addressing the execution and realisation of interventions in a pre-existing operational context such as a healthcare setting, where novel interventions must fit into deeply embedded professional and organisational systems. NPT will be used to develop the topic guides for interviews and focus groups and provide the framework for analysis. NPT is explicitly concerned with the workability and sustainability of complex interventions. NPT can therefore be used to address the feasibility of implementation, by recognising which components of implementation may be particular barriers or facilitators by examining the extent to which the intervention can become integrated into everyday practice.^29^ These data will support a deeper understanding of the acceptability of the intervention, and the resources needed, and disclose potential barriers and facilitators from the participants’ and healthcare professionals’ points of view.

#### Cost analysis

The objective of the cost analysis will be to assess the relative cost of the clinical staff from the number, type and duration of appointments performed by the case manager, therapists and mental health specialist. Costs will be calculated using the National Cost Index^30^ for the NHS.

### Monitoring

#### Trial steering committee

Independent supervision of the trial will be carried out by members of the Trial Steering Committee (TSC). The TSC will have responsibility for monitoring the progress of the trial, engagement with the protocol, patient safety and consideration of new information. The TSC will include the chief investigator, principal investigators and three independent chairs (patients). The trial statistician will attend when appropriate. The chief investigator will oversee the overall management of the trial. The principal investigator ([name]) will be responsible for the coordination of the study on site and will carry out the day-to-day activities involved in running the trial at each site. Delivery of collaborative care will be carried out by a designated skilled case manager ([name]).

#### Suicidal ideation and risk of self-harm protocol

Suicidal ideation might be identified by the PHQ-ADS, which asks specifically about thoughts of self-harm. Participants might also disclose this ideation at any point during the study, from recruitment to discharge.

At present, patients may have these thoughts but are not assessed or asked about them. There is strong evidence to suggest that asking patients about suicidal thoughts does not increase risk but may be protective.^31^ Should participants disclose suicidality, the protocol outlined below will be followed.

For any participant scoring 1 or higher on question 9 of the PHQ-ADS (‘Thoughts that you would be better off dead or of hurting yourself in some way’), the research team will discuss these thoughts with the patient and ask them to answer the Columbia-Suicide Severity Rating Scale Screen Version (C-SSRS Screen). The C-SSRS Screen^32^ is a validated 6-item assessment scale for people with suicidal ideation. It categorises patients into low, medium and high risk. For example:
passive thoughts such as wishing to be dead with no further risk indicators are considered low riskmethods and plans, or active thoughts such as wishing to cause self-harm, are considered a moderate risksuicidal intent and any suicidal behaviour in the past 3 months indicate a high risk.

All triggers of the suicidal ideation and risk of self-harm protocol and the actions that are taken in response will be recorded on the Research Risk of Self-Harm form and clinical notes.

#### Suicidal thoughts before randomisation, during usual care or at the end of study interviews

The research team will inform the named clinician responsible for the participant's care of their level of risk. It is standard practice within the RNOH Trust that all thoughts of self-harm should be discussed with the RNOH Psychiatry Service. The RNOH Psychiatry Service will assess the participant and, depending on the level of risk, offer advice or refer for treatment and inform their GP. Participants will also be signposted to the Rethink Mental Illness online resources website, which provides information on coping with suicidal thoughts.

For participants who reveal suicidal thoughts for the first time during the end-of-study interview and are no longer under the care of the RNOH out-patient services, or for participants who refuse to be referred to the RNOH Psychiatry Service, the research member will discuss the participant's presentation with the chief investigator, who is a consultant psychiatrist, within 24 h.

#### Suicidal thoughts reported by participants in the intervention group

If suicidal thoughts emerge in a participant allocated to the intervention group, the case manager will assess the risk clinically, supported by the C-SSRS Screen tool. The research team will then ask for the participant's consent to make a referral according to the risk level:
participants deemed to be at low risk will be flagged up to their GPparticipants at moderate risk will be offered triage and risk assessment by the hospital psychiatrist within 1 week of referralparticipants at high risk will be assessed immediately by the hospital psychiatrist.

If a participant at moderate or high risk of self-harm refuses to be referred, the case manager will discuss the participant's presentation with the chief investigator. This will be immediately for high-risk participants, within 24 h for moderate-risk participants and within 48 h for low-risk participants (Fig. 2).

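### Self-harm procedure, intervention arm: the trigger for escalating a refused referral names moderate and high risk, but the time limits that follow also cover low risk

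*Protocol article*

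**What the plan says.** Under the heading on suicidal thoughts reported by intervention-group participants, the case manager first assesses the risk clinically, supported by the C-SSRS Screen. The research team then asks for the participant's "consent to make a referral according to the risk level". Low risk leads to a flag to the GP, moderate risk to an offer of psychiatric triage within a week of referral, and high risk to immediate psychiatric assessment.

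The refusal rule follows. Its condition is "If a participant at moderate or high risk of self-harm refuses to be referred"; in that event the chief investigator is to hear of the case from the case manager. The sentence after it gives the timing: at once for high risk, 24 h for moderate risk, and "within 48 h for low-risk participants". That sentence ends with a reference to Fig. 2.

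The section just before it covers suicidal thoughts before randomisation, during usual care or at end-of-study interviews. It has its own refusal rule, "for participants who refuse to be referred to the RNOH Psychiatry Service", with discussion within 24 h and no distinction by risk level. It also records as standard Trust practice that "all thoughts of self-harm should be discussed with the RNOH Psychiatry Service".

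**The concern.** Two adjacent sentences govern the same act and do not cover the same people. The first makes the discussion with the chief investigator depend on moderate or high risk. The second gives low-risk participants a deadline for it. Staff could read the rule in two ways, one leaving out low-risk refusals and the other escalating them within 48 h.

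This is an operative safety instruction, not background text. The general self-harm section places passive thoughts, including a wish to be dead without further indicators, in the low-risk class. If the trigger were followed to the letter, the intervention-arm rule would not send a low-risk participant who refused the GP flag on to the chief investigator, and the GP would not have been told either.

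**Working it through.** There is no figure to reproduce. The check sets the provisions for the intervention arm side by side.

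| Risk level | Action for which consent is sought | Named in refusal trigger? | Deadline for discussion with chief investigator |
|---|---|---|---|
| High | Immediate psychiatric assessment | Yes | Immediately |
| Moderate | Psychiatric triage within 1 week of referral | Yes | 24 h |
| Low | Flag to GP | No | 48 h |

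**Step 1: compare the two sets.** The trigger covers {moderate, high}, 2 of 3 levels. The deadlines cover {high, moderate, low}, 3 of 3. The difference is {low}. High and moderate risk are consistent.

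**Step 2: could the deadlines belong to another act?** If they timed the referral or assessment, moderate risk would have both 24 h and 1 week, and the GP flag has no time attached to it elsewhere. The deadlines fit only the discussion with the chief investigator, so this reading does not remove the mismatch.

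**Step 3: can a low-risk participant refuse?** The GP flag is listed beneath the request for "consent to make a referral according to the risk level", so consent can be withheld at that level. A 48 h low-risk deadline after refusal would also have no use if low-risk refusal could not occur.

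**Step 4: does the preceding section settle it?** Its heading limits its refusal rule to other situations, and the refusal it addresses is of a psychiatry referral, not of a GP flag. The absence of a risk-level restriction there supports the inclusive reading here, but it does not supply the missing trigger.

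**Step 5: how many could be affected?** The sample size section states: "We aim to recruit 40 patients in total, with 20 randomised to each arm". The ceiling is therefore 20 of 40 participants (20/40 = 50%, which is simply the allocation ratio). Those touched are the subset of the 20 who report suicidal thoughts, are classed as low risk and refuse the GP flag. The article gives a rate for none of these, so only the ceiling can be stated. The subset is probably small.

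**The case against.** The strongest reply is that the two sentences can be read together as one workable rule. The trigger does not say that moderate and high risk are the only levels escalated; that restriction is an inference from what it names. A case manager who reads on meets an explicit 48 h instruction for low risk and would have to disregard it to leave such a participant out. This largely stands: the intended rule is recoverable, which is why the point is minor. It does not make the two sentences agree.

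A reader might go further and infer that a low-risk refuser gets no escalation or follow-up at all. The article does not support that. The practice that "all thoughts of self-harm should be discussed with the RNOH Psychiatry Service" appears under a heading for other situations but is worded as Trust-wide, with no limit by arm or risk level. The case manager's clinical assessment and the monthly questionnaire monitoring continue, the case manager can refer for psychological or psychiatric support, and "All triggers of the suicidal ideation and risk of self-harm protocol and the actions that are taken in response will be recorded". What is left uncertain is one specific step, discussion with the chief investigator.

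It can also be said that Fig. 2 and the risk-of-self-harm form may state the rule correctly. They may, and for that reason nothing is claimed here about what staff will actually do. A correct figure would show which version is meant but would not repair the printed text.

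**Conclusion.** The section is internally inconsistent. The escalation trigger omits low risk while the deadlines include it. One of three risk levels is affected, in one arm, and only where the GP flag is refused. The probable slip is the restriction in the trigger, because the 48 h deadline serves no purpose otherwise and the neighbouring refusal rule has no such restriction. That judgement rests on the text alone, with Fig. 2 unseen.

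Severity is minor. The meaning can largely be recovered and other safeguards remain. No feasibility estimate, outcome, sample size or analysis is touched. The point is still worth correcting because it sits in a patient-safety rule and the remedy is a single phrase.

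**What to change.** In the refusal sentence, replace the reference to moderate or high risk with *at any risk level*, so that every refused referral, including a refused GP flag, goes to the chief investigator. Keep the graded deadlines as they are: immediately, 24 h and 48 h. Check that Fig. 2 shows the same rule and tell the case manager which reading applies.

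Deleting the 48 h low-risk deadline would also make the sentences consistent. Widening the trigger is preferable because it keeps the stated timetable, matches the neighbouring section and is the safer choice.

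The cost is one phrase, one figure check and a short note to the case manager, with no extra staff, visits or data.
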